## Methods

### Design

The trial, termed EFFORT-ICU, is a phase II feasibility trial incorporating a mixed methods design. The study follows the guidelines for feasibility trials outlined by the SPIRIT 2013 Statement [39]. EFFORT-ICU is a prospective single-centre, single blinded, equally randomised controlled trial (1:1) comparing standard occupational therapy care to an early enhanced occupation-based therapy. A study overview is shown in Fig. 1. The trial is registered as follows: Australia New Zealand Clinical Trials Registry (ANZCTR): ACTRN12618000374268; prospectively registered on 13 March 2018/https://www.anzctr.org.au.

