### Outcome measures

#### Primary outcome measure

Independence within activities of daily living will be measured using the Functional Independence Measure (FIM™). The FIM will quantify the participant’s functional and cognitive status at intensive care unit and hospital discharge, as well as at 90 days post-randomisation. This tool is validated for use in the critically ill population [60, 61] and provides reliable information regarding patient functional change during rehabilitation across various hospital and community settings [62]. The FIM will be conducted within 24 h of the expected discharge from the intensive care unit and hospital or on the Friday before the expected discharge, if likely to occur over the weekend. It will also be administered during the 90-day follow-up session. The FIM will be performed by an occupational therapist blinded to participant assignment groups and who does not actively work on the intensive care unit.

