### Sample size

A sample size of 30 participants has been chosen, based on recommendations regarding pilot and feasibility trials evaluating outcomes [77]. Fifteen patients from the intervention group will be included within the qualitative component carried out at 90 days post-randomisation.

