### Data analysis

All data from the case report forms (CRF) will be entered into a purposefully designed Excel database and exported into SPSS version 22.0 for analyses. Descriptive statistics will be used to determine the distributions of the data for the intervention and control groups and to test whether statistical assumptions for parametric tests are achieved. Imputation will be used to correct for missing data. Continuous variables that are normally distributed will be compared between the groups at each follow-up using an independent groups *t* test. Effect sizes will be calculated using Cohen’s *d*. Non-parametric analysis will be conducted for continuous variables that are not normally distributed. Categorical variables will be compared with the chi-square statistic. A *p* value of 0.05 will be considered statistically significant. Where appropriate, analyses will be reported with mean differences and 95% CI. Previous values from the same patient will be used for missing data.

In particular, objectives will be analysed as follows:
The utility of the selection of outcome measures will undergo sensitivity analyses in relation to the ease with which they can be administered and will relate to missing data and the identification of both univariate and multivariate outliers. The effect size for the primary outcome variable will be used to determine the required sample size for a fully powered trial.Recruitment and consent rates will be collected and analysed to determine the feasibility of recruiting form the chosen population. The inclusion and exclusion data (screening log) will be summarised and will influence further protocol changes when considering progression to a full scale randomised controlled trial.Retention rates in response to follow-up procedures (attendance at interviews) will be analysed to identify any trends that may influence further trial progression.The intervention data will undergo sensitivity analyses in relation to non-compliance, the intention to treat per protocol in addition to as treated. Protocol violations regarding the intervention manual strategies will be noted.The intervention effect will be analysed through the use of the above outcome measures, and further analysis of case notes will reveal common trends in treatment adaptation or selection, based on the structure of the intervention manual.

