## Discussion

Early rehabilitation within critical care units has been shown to be effective in multiple studies [17, 24]; however, the occupational therapy approaches to enhance long-term recovery require further investigation especially in mechanically ventilated patients. This trial aims to explore the feasibility of providing occupational therapy to mechanically ventilated patients in a critical care setting. It aims to identify approaches that may be beneficial to patients and family members surviving a critical care stay, as well as defining where priorities in service provision may lie. The ability to optimise recovery with clearer multidisciplinary input may strengthen future collaboration to drive an early rehabilitation model. Analysis of day to day therapy provision, the ability to adapt and engage patients along a continuum of sedation and immobilisation variables will provide clarity about the types of interventions that are best completed in the critical care setting by an occupational therapist. While this study is not powered to detect clinically significant change, it will provide information that will enable the design of a phase III trial including sample size calculations. A dissemination plan has been developed that includes publication in peer-reviewed journals, webinars and conference presentations and posters.

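### The phase III sample size is to be set from the FIM effect size observed in this 30-patient pilot, which is too imprecise for that use

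*Protocol article*

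**What the plan says.** The primary outcome is the FIM. The Primary outcome measure section has it quantify "functional and cognitive status at intensive care unit and hospital discharge, as well as at 90 days post-randomisation", and the Data analysis section compares the groups at each follow-up. No visit is singled out.

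On the metric, Data analysis states "Effect sizes will be calculated using Cohen’s" *d*. Under the first objective it then fixes the use of that figure: "The effect size for the primary outcome variable will be used to determine the required sample size for a fully powered trial". No qualification is attached, such as a confidence limit, a shrinkage factor or a minimum important difference.

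The Sample size section reads "A sample size of 30 participants has been chosen, based on recommendations regarding pilot and feasibility trials evaluating outcomes". The Design section gives equal allocation.

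Two other places bear on the rule. The Discussion concedes that "this study is not powered to detect clinically significant change", but the same sentence goes on to say that the study will support the phase III sample size calculation. The section on progression criteria projects a full trial of 100 to 150 patients, with reference to clinical significance and a cited study. It gives no FIM target difference.

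**The concern.** A standardised difference from 15 or fewer patients per arm is mostly sampling error. The required sample size varies with the inverse square of *d*, so that error is magnified when *d* goes into a sample size formula. A *d* that is high by chance gives a phase III trial with too little power. A *d* that is low by chance gives an impractically large one, and a *d* at or below zero gives no usable size at all.

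The missing visit adds to this. ICU discharge, hospital discharge and 90 days give three candidate values of *d*, and the rule does not choose between them.

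What is at stake is the power of the later trial. The conduct of this pilot and its feasibility results are not affected.

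**Working it through.** **Inputs from the protocol article.** N = 30 at 1:1, so 15 per arm (Sample size; Design). Retention target 75% (Table 1), so 0.75 × 15 = 11.25, taken as 11 per arm. Significance level 0.05 (Data analysis). The article does not state sidedness, so two-sided is assumed.

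**Inputs not in the documents.** True *d*: assumed 0.5, with range 0.3 to 0.8. Phase III target power: assumed 80%, with 90% as the variant.

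**The plan's own figure.** The 30 rests on a cited recommendation, with no effect size, SD or precision target, so there is nothing to reproduce. For orientation, 15 per arm has power Φ(0.5 × √7.5 − 1.96) = 0.28 for *d* = 0.5, in line with the Discussion's concession.

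**Is a *d* of 0.5 reasonable?** At 80% power the detectable *d* is (1.960 + 0.842)/√(n/2). The projected 100 to 150 patients are 50 to 75 per arm, which gives 2.802/√25 = 0.56 and 2.802/√37.5 = 0.46. The central assumption therefore fits the protocol's own projection.

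**Precision of the pilot's *d*.** SE(*d*) = √(2/n + *d*²/(4n)). For an observed *d* of 0.5:
- 15 per arm: SE = √(0.1333 + 0.0042) = 0.371; 95% CI 0.5 ± 1.96 × 0.371 = -0.23 to 1.23.
- 11 per arm: SE = √(0.1818 + 0.0057) = 0.433; 95% CI -0.35 to 1.35.

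**What this does to the sample size.** With a two-sample *t* test at 80% power, *d* = 0.5 needs 64 per arm. One SE either side at 15 per arm means *d* = 0.87, needing about 22 per arm, or *d* = 0.13, needing about 930 per arm.

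**Chance of a badly underpowered trial.** A trial sized on the observed *d* has true power below 50% when the observed *d* exceeds the true *d* by the factor (1.960 + 0.842)/1.960 = 1.43 at 80% target power, or (1.960 + 1.282)/1.960 = 1.65 at 90%. For true *d* = 0.5, 15 per arm and 80% target power, the normal approximation gives P(observed *d* > 0.715) = 1 − Φ(0.215/0.371) = 0.28. Simulating 1,000,000 pilots per scenario (observed *d* from a noncentral *t*) gives:

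| True *d* | Target power | 15 per arm | 11 per arm |
|---|---|---|---|
| 0.3 | 80% | 0.37 | 0.39 |
| 0.5 | 80% | 0.28 | 0.31 |
| 0.8 | 80% | 0.20 | 0.24 |
| 0.3 | 90% | 0.30 | 0.33 |
| 0.5 | 90% | 0.19 | 0.23 |
| 0.8 | 90% | 0.10 | 0.14 |

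**Chance of no usable size.** P(observed *d* ≤ 0) at true *d* = 0.5 is about 0.09 (15 per arm) to 0.12 (11 per arm).

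None of these figures allows for a choice among the three visits.

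**The case against.** The strongest reply is that the rule would not be applied mechanically. The Discussion admits the lack of power, Data analysis plans mean differences with 95% confidence intervals where appropriate, and the progression section already projects 100 to 150 patients. If 50 per arm acted as a floor, power at *d* = 0.5 would be Φ(0.5 × √25 − 1.96) = 0.71, and the under-50% outcome would disappear for that effect. This carries some weight, but the article does not call the projection a floor, and at *d* = 0.3 the same 50 per arm gives only Φ(0.3 × √25 − 1.96) = 0.32. Neither the projection nor the admission withdraws the sizing rule.

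A second reply is that 30 is an ordinary pilot size. That is not disputed here. The objection is to the use made of *d*.

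Several stronger readings are tempting and should not be drawn:
- That three trials in ten will be badly underpowered, as a plain fact. That figure depends on a true *d* near 0.5 and 80% target power, neither of which is in the documents.
- That this number is the pilot's main product. The objectives also cover utility of the measures, recruitment and consent, retention and fidelity, and exploration of effect is listed last in Part 1.
- That a low *d* would end the programme. Table 1 contains no effect-size criterion, so a low *d* triggers no stop. At most it produces an impractical size.
- That the most favourable visit will be picked. The wording leaves room for that but does not plan it.

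**Conclusion.** The point holds as a should-fix. As written, the rule sizes a definitive trial on an estimate whose confidence interval runs from harm to a very large benefit, and it does not name the visit.

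The probability of a phase III trial with under 50% true power is about 0.28 to 0.31 in the central case (true *d* 0.5, 80% target power, two-sided 0.05) and about 0.10 to 0.39 over the range examined. It assumes that the observed *d* alone fixes the size. The interval around *d* depends on neither the true effect nor the target power, and it is enough by itself to make the rule unsuitable.

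It is not more severe than that because the rule governs a later trial. It does not touch this pilot's participants, feasibility results or progression decision, and it can be replaced before phase III is designed.

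**What to change.** Replace the sentence in Data analysis with:

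> The phase III sample size will be based on a minimum important difference in FIM at one named visit (90 days post-randomisation, the only one at a fixed time from randomisation), justified independently of this pilot's between-group results and fixed before those results are analysed. From this pilot only the pooled SD (upper one-sided 80% confidence limit) and the retention rate will be used. Cohen's *d* will be reported with its 95% CI as description only.

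The timing is tied to the analysis of between-group results because the research team is unblinded and recruitment has already begun. Variance explained by baseline covariates is left out on purpose: from 22 to 30 patients it would be another imprecise estimate, and Table 4 shows no baseline FIM. The progression section should then say how the 100 to 150 projection relates to this calculation.

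**Cost.** No extra patients or data are needed in this pilot. The documents contain no important difference for the FIM, so one must be justified from outside it, which is more work than rewording a paragraph. The SD limit also raises the planned phase III size. The factor on the sample size is df/χ²(0.20, df): 28/21.59 = 1.30 with 15 per arm, and 20/14.58 = 1.37 with 11 per arm (on the SD itself, 1.14 and 1.17). As an illustration, a target equal to 0.5 of the pilot SD needs 63 per arm at 80% power by the normal approximation. With the limit this becomes about 82 per arm (63 × 1.30) or about 86 (63 × 1.37).

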### Progression criteria to decide whether to proceed with RCT

As randomised controlled trials involve a significant organisational and financial input, the decision to progress from a pilot study requires clear and objective measures to ensure that staffing and patients benefit from participation in a study. The use of the guidelines and key information to consider, as proposed by Avery et al. (2017) [41], will influence the evaluation as to whether the trial should progress. The criteria for progression have been identified while considering the usual trial length for a grant funded study (2–3 years), with a projected trial recruitment of 100–150 patients to ensure improvements in clinical significance is achieved [24]. Targets for retention (75%) outcome measure administration (80%) and intervention completion (50%) were identified to minimise impact of missing data while aligning with clinical expectations for this cohort of patients (Table 1).

**Table 1 Tab1:** Progression criteria for RCT

Domain	Proceed with RCT	Proceed with changes to protocol	Do not proceed unless problem resolution
Recruitment	Recruitment of 30 eligible patients within 6 months	Recruitment of eligible patients within 6–12 months	Unable to recruit 30 patients in 12 months
Retention	Minimum of 75% retention to follow-up	Minimum of 50 % retention to follow-up	Less than 50% retention to follow-up
Completion of intervention	At least 50% complete intervention for 40–60 min per day	At least 50% complete intervention for 20–40 min per day	Less than 50% complete intervention for 20 min per day
Outcome measures acceptability	Able to administer 80% of the outcome measures at each time point	Able to administer 80% of the outcome measures at each time point	Able to administer 80% of the outcome measures at each time point
Adverse events	No serious therapy-related adverse events during trial	Less than 5 serious therapy-related adverse events during trial	Five or more serious therapy-related adverse events during trial

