#### Qualitative follow-up

Part 2 of this study includes a qualitative component and will be guided by interpretive description [58] to explore the lived experience of participants receiving the intervention and the perception of family members or the most involved significant other. At 90 days post-randomisation, all patients from the early enhanced occupation-based therapy group will be invited to participate in in-depth semi-structured interviews targeted towards exploring their experience of engaging within the early enhanced occupation-based therapy. In the event that the participant is too unwell to physically attend an interview, alternative arrangements, such as telephonic interview, will be offered.

The person responsible will be provided with a separate information and consent form to participate in the interview.

Interviews will be conducted by the principal researcher in a private, wheelchair accessible room at Logan Hospital. Funding for transport will be provided to facilitate attendance at interviews. Wheelchair accessible transport will be organised for participants who require specialist accessibility options. Interviews will be audiotaped and transcribed verbatim by a transcription service.

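### Retention is defined as interview attendance, which only intervention patients can supply; the 75% and 50% progression limits have no denominator, and the 15 planned interviews allow for no attrition

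*Protocol article*

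**What the plan says.** All references are to the protocol article.

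- **Definition.** The third Part 1 objective (Aims and objectives) explains retention, in parentheses, as interview attendance. The matching item under Data analysis repeats this and links it to progression: "Retention rates in response to follow-up procedures (attendance at interviews) will be analysed to identify any trends that may influence further trial progression".
- **Who is interviewed.** Under Qualitative follow-up, at 90 days "all patients from the early enhanced occupation-based therapy group will be invited to participate in in-depth semi-structured interviews". Significant others are approached separately. A telephone interview is possible for a participant too unwell to come in. No interview is described for control patients.
- **Progression limits.** The retention row of Table 1 reads "Minimum of 75% retention to follow-up" for proceeding and "Minimum of 50 % retention to follow-up" for proceeding with changes; below 50% the trial should not go ahead unless the problem is resolved. The row names no arm, denominator or type of contact.
- **Interview numbers.** The Sample size section sets a total of 30 and adds: "Fifteen patients from the intervention group will be included within the qualitative component carried out at 90 days post-randomisation". The Design section gives 1:1 allocation.

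**The concern.** A feasibility trial exists largely to supply the figures for a go/no-go decision, and retention is one of five domains in Table 1. The article explains only once, in two places with the same gloss, what its retention rate counts, and that explanation describes an event that cannot occur in the control arm. Followed literally, a control patient can be neither retained nor lost.

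Even within the intervention arm, interview attendance and outcome follow-up are different things. A telephone interview would count as attendance although a dynamometer reading cannot be taken by telephone. Conversely, a patient who completes the Functional Independence Measure (FIM) but declines the interview would count as lost.

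A phase III trial needs to know how many patients in each arm provide the 90-day outcome, and whether loss differs between arms. A rate from one arm answers neither question and rests on half the patients.

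The planned fifteen interviews raise a smaller, related point. That number assumes complete retention of one arm, in a plan that treats 75% as success and lists attrition as a risk under Limitations.

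**Working it through.** **Inputs.** Total 30 (Sample size); allocation 1:1 (Design); limits 75% and 50% (Table 1); 15 interviewed intervention patients (Sample size).

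**Step 1: the plan's figure of 15.** 30 × 1/2 = 15. The figure reproduces as the whole expected intervention arm, with nothing deducted for death, withdrawal, refusal or loss.

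**Step 2: the limits as counts.**
- All randomised: 0.75 × 30 = 22.5, so 23 of 30; 0.50 × 30 = 15 of 30.
- Intervention arm only: 0.75 × 15 = 11.25, so 12 of 15; 0.50 × 15 = 7.5, so 8 of 15.

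**Step 3: the two readings on the same data.** For illustration, suppose that every intervention patient followed up is interviewed, and that nobody else is.

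| Intervention followed up | Control followed up | Interviews only | All randomised |
|---|---|---|---|
| 15/15 | 7/15 | 100%, proceed | 22/30 = 73%, changes |
| 12/15 | 7/15 | 80%, proceed | 19/30 = 63%, changes |
| 12/15 | 8/15 | 80%, proceed | 20/30 = 67%, changes |
| 12/15 | 2/15 | 80%, proceed | 14/30 = 47%, stop unless resolved |
| 11/15 | 12/15 | 73%, changes | 23/30 = 77%, proceed |

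The last row shows that the readings can also differ in the other direction. With 12/15 in the intervention arm, the interview reading is 80% whatever happens to controls, while overall retention can lie anywhere from 12/30 (40%) to 27/30 (90%).

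**Step 4: precision.** Exact 95% intervals at the smallest passing counts are 58% to 90% for 23/30 and 52% to 96% for 12/15. If both arms had the same true retention of 60%, the proceed limit would be met with probability 0.044 on 30 patients and 0.091 on 15. At a true 85% it would be met with probability 0.930 and 0.823.

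**Step 5: fifteen interviews.** The expected number is 15 × p, and the probability that all 15 are retained is p^15 if losses are independent.
- p = 0.75: 11.25 expected; 0.75^15 = 0.013
- p = 0.90: 13.5 expected; 0.90^15 = 0.21
- p = 0.95: 14.25 expected; 0.95^15 = 0.46

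To expect 15 interviews at 75% retention would need 15/0.75 = 20 intervention patients. The documents give no expected attrition rate, so these values of p are assumptions; 75% is the plan's own proceed limit.

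**The case against.** A reader might infer that the 75% criterion itself leaves out the control arm, or that controls are not followed up. The article does not support either.

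- The Table 1 row mentions neither interviews nor an arm, and the text above it says the targets were chosen to limit missing data, which concerns both arms.
- Data collection records withdrawals and their reasons as retention data, without restriction by arm.
- Table 4 and the outcome sections schedule 90-day measures for participants generally, and Data analysis compares the groups at each follow-up.
- The exclusion of interstate patients who could not attend the 90-day visit in person applies before randomisation.

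A both-arm reading of Table 1 is therefore open, and perhaps intended. That limits the finding without removing it: the article's only explanation of what the retention rate counts is the interview one, and Data analysis ties it to progression. This is a definition that is stated and badly fixed, not a detail left to a fuller document.

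On missing outcomes, Table 1 has a separate row for outcome-measure administration, so the 90-day measures are not ignored. That row does not repair the retention definition.

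A reader might also infer that paid travel favours one arm. The statement "Funding for transport will be provided to facilitate attendance at interviews" stands in a section on interview logistics. The article does not say whether control patients receive travel support for their 90-day visit, so unequal support would be inferred from silence and is not part of this point.

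On the fifteen interviews, all intervention patients are to be invited, so 15 works in practice as a maximum, and no progression limit or planned analysis depends on reaching it. This objection stands: the fault there is in the wording, not a failure of design.

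**Conclusion.** The point holds as an inconsistency. Retention is described as attendance at an interview offered to one arm, while the progression limits refer to follow-up in general and give no denominator. If the stated definition is applied to Table 1, control losses are not counted and the outcome can move between categories, as with 100% against 73%, or 80% against 63% or 67%. If Table 1 is read as covering all randomised patients, the limits are usable, but the objective and its analysis then measure something else.

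The interview target is unrealistic as worded: about 11 are expected at 75% retention, with a 1.3% chance of all 15.

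The figures assume exactly 15 patients per arm. The article does not describe blocking, so the arms may differ slightly in size. The probabilities also assume independent losses. The severity is should-fix: the go decision can depend on the ambiguity, but a both-arm reading is available and the remedy is simple.

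**What to change.** - In the third Part 1 objective, the retention row of Table 1 and the matching Data analysis item, define retention as completion of the 90-day assessment (for example the FIM) among all randomised participants, overall and by arm. Show deaths and withdrawals separately, and apply the 75% and 50% limits to the overall figure. An alternative denominator, such as patients alive at 90 days, could be defended; what matters is that one is stated before progression is judged.
- Remove the interview parenthesis from the retention wording and report interview uptake as a separate Part 2 figure.
- In Sample size, replace the fixed fifteen with up to 15, about 11 expected at 75% retention.

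The cost is rewording in four places, plus the ethics approval and registry notification that the Ethics/governance section requires for protocol changes. The downside is a stricter retention figure, since deaths and control losses now count against it. Recruitment was paused when the article appeared, so the definition can be settled before progression is judged. If the full protocol on the registry already defines retention in this way, only the article's wording needs to be brought into line.
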